### Randomization and allocation

This study will use a stratified block randomization method, with stratification factors including age (≤60 years vs. >60 years) and disease duration (≤3 months vs. >3 months). A statistical specialist not involved in clinical procedures or outcome assessments will generate the random sequence using R software. The 160 participants will be allocated in a 1:1 ratio to the taVNS group (*n* = 80) or the sham stimulation group (*n* = 80). To conceal allocation, the random sequence will be placed in sequentially numbered, opaque, sealed envelopes. Researchers will open the envelopes in strict order of participant enrollment and will meticulously record the date, time, and signature of the person opening each envelope.

### Allocation and blinding

This study employs a partial blinding design: participants, responsible clinicians, outcome assessors, and statistical analysts will remain blinded to group allocation, while the intervention providers cannot be blinded due to the visibility of the stimulation site (auricular concha). The intervention providers, rehabilitation therapists, responsible clinicians, and outcome assessors are independent personnel with separate roles; rehabilitation therapists are responsible for conventional rehabilitation training and are not involved in study assessments. An independent research coordinator, who is fully aware of the group allocation, will be responsible for random assignment and allocation concealment. In the event of a serious adverse event, the responsible clinician will decide whether to unblind, and will record the time, reason, and signature of unblinding. The unblinding information will be disclosed only to the extent necessary for treatment. The rehabilitation therapists will remain blinded to group allocation; they will adjust rehabilitation intensity solely based on Brunnstrom stage and modified Barthel Index scores, and will not be involved in the administration of taVNS or sham stimulation, nor have access to group allocation information.

To evaluate the effectiveness of blinding, at the end of each week during weeks 1 to 4 (once per week), a research assistant who is not involved in treatment administration will ask each participant: “Do you think you received active stimulation or sham stimulation in this session?” The response options are active stimulation, sham stimulation, or uncertain. The participant's confidence in their answer will be recorded on a 10-point scale. For analysis, responses of “uncertain” will be excluded, and the proportion of correct guesses will be calculated based only on the two definitive responses (“active stimulation” or “sham stimulation”) as the number of correct guesses divided by the total number of definitive responses. A binomial test will be used to determine whether this proportion is significantly higher than 50% (*α* = 0.05). The proportion of “uncertain” responses will be reported separately as a supplementary indicator of blinding uncertainty. If the correct guess rate at all time points is close to 50%, blinding will be considered successful. If the correct guess rate at any time point is significantly higher than 50%, it will suggest potential blinding failure; this result will be used to quantify the potential impact of expectancy bias (e.g., on CPET performance), considered in the interpretation of the final results, and reported as a limitation. It should be emphasized that this assessment is intended only to monitor blinding effectiveness and cannot substitute for a credible sham stimulation design.

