### Intervention

A transcutaneous auricular vagus nerve stimulation device manufactured by Jiangxi Jingyi Medical Technology Co., Ltd., China, will be used. Stimulation electrodes will be placed over the vagus nerve distribution hotspot in the left auricular concha (23, 24). The stimulation parameters are: biphasic square wave, frequency 25 Hz, pulse width 200 µs, single session duration 30 min (25). The stimulation intensity will be individually adjusted based on each participant's sensory threshold. The sensory threshold is defined as the minimum current intensity at which the participant first clearly perceives a tingling sensation on the skin surface (starting from 0.1 mA and increasing slowly). The stimulation intensity in the active taVNS group will be set at a level that is just at or slightly above the sensory threshold (i.e., an intensity that the participant can clearly perceive without pain), typically between 0.5 and 1.5 mA, to ensure a clear, comfortable, and non-painful stimulation sensation. Treatment will be administered once daily, five days per week, for a total of 4 weeks. The sham stimulation group will use the same device, electrode placement, and operational procedures as the active stimulation group. Consistent with previous studies (25), the stimulation current will be set to 0 mA throughout the entire 30 min session. The indicator lights and buzzer sounds of the device will be synchronized with those of the active stimulation group throughout the treatment period.

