### Statistical methods

Statistical analyses will be performed using SPSS 26.0 and R 4.1.0, following the intention-to-treat principle. All tests will be two-sided, with a significance level of *α* = 0.05 unless otherwise specified for multiple comparisons. Statisticians will remain blinded to group allocation until data lock. All randomized participants will be retained in the intention-to-treat analysis. The per-protocol analysis will report the proportion and characteristics of participants who do not meet the effort criteria. Additional stratified analyses will be considered: (1) all randomized participants; (2) those meeting adequate-effort criteria; (3) those terminating due to cardiopulmonary limitation; and (4) those terminating due to neurological or motor limitation, to assess the robustness of the results. For the primary outcome, VO_2_peak will be analyzed using a linear mixed-effects model, with group, time, and their interaction as fixed effects and participant as a random effect (random intercept) to account for within-subject correlations; a random slope may be added if model fitting requires. Age, sex, baseline VO_2_peak, stroke type, disease duration, baseline National Institutes of Health Stroke Scale score, and recruitment source (hospital or community) will be included as prespecified covariates. In the model, the time factor (T0, T1, T2) is used to estimate longitudinal trends, while baseline VO_2_peak is included solely as a covariate to adjust for baseline differences; the two serve different functions and do not constitute redundant adjustment. The covariance structure will be selected from unstructured, compound symmetry, or first-order autoregressive models based on the Akaike information criterion or Bayesian information criterion. The primary treatment effect will be assessed based on the baseline-adjusted between-group difference in VO_2_peak at T1, and the effect estimate, 95% confidence interval, and corresponding *p*-value will be reported. For secondary outcomes, all four measures (interleukin-6, tumor necrosis factor-alpha, National Institutes of Health Stroke Scale, and modified Barthel Index) will be analyzed longitudinally using the same linear mixed-effects model as for the primary outcome. For variables with substantial deviation from normal distribution or violations of parametric assumptions, generalized linear mixed models or nonparametric methods will be used as supplements. To control for multiple comparisons, a Bonferroni correction will be applied for the four secondary outcomes, with the significance threshold set at *α* = 0.05/4 = 0.0125. The exploratory outcome (heart rate variability) will not be adjusted for multiple comparisons and will be used only for exploratory interpretation. For missing data, the primary analysis will use the linear mixed-effects model under the missing-at-random assumption, utilizing all available observed values. To assess robustness, multiple imputation by chained equations and per-protocol analysis will be conducted as sensitivity analyses. In addition, the originally prespecified repeated-measures analysis of variance will be performed as a complementary analysis for comparison with the primary results; if the sphericity assumption is violated, the Greenhouse-Geisser correction will be applied, and *post-hoc* comparisons will be performed using the Bonferroni method. The incidence of adverse events will be compared using Fisher's exact test. If the sample size permits, prespecified exploratory subgroup analyses will be conducted for stroke type (ischemic vs. hemorrhagic) and recruitment source (hospital vs. community), using interaction tests to assess potential effect modification, with results interpreted only as exploratory. Due to sample size constraints (80 participants per group), stratification was performed only for age and disease duration. Other heterogeneity factors, including stroke type, baseline NIHSS score, and baseline VO_2_peak, have been incorporated as prespecified covariates into the linear mixed-effects model for adjustment.

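### The blinding check judges one pooled correct-guess rate against 50%, a reference that isolates a difference in belief only if both arms give equally many definite answers

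*Protocol article*

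**What the plan says.** The Protocol article, under Allocation and blinding, has each participant asked at the end of each of weeks 1 to 4 whether the stimulation was active or sham, with *uncertain* as a third answer. The analysis is fixed in the text:

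- *Uncertain* answers are left out and reported separately as a supplementary indicator. The statistic is correct guesses divided by all definite answers; no rate per arm is defined.
- "A binomial test will be used to determine whether this proportion is significantly higher than 50" per cent, at α = 0.05, each week.
- A significant excess in any week suggests blinding failure. In the other direction: "If the correct guess rate at all time points is close to 50%, blinding will be considered successful". No margin is attached and no adjustment for four tests is stated.

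The same section says that "participants, responsible clinicians, outcome assessors, and statistical analysts will remain blinded to group allocation". Under Intervention, the active current is set at "an intensity that the participant can clearly perceive without pain", while in the sham arm "the stimulation current will be set to 0 mA throughout the entire 30 min session", with lights and sounds matched. Limitations concedes that differences in sensation may let participants guess their group.

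**The concern.** VO2peak comes from a symptom-limited test with verbal encouragement, so expectancy is a serious rival explanation for a positive result. The article itself names expectancy bias on exercise-test performance and says the guess rate will be used to quantify it. What matters for the treatment contrast is how belief differs between the arms, and a single pooled rate does not estimate that difference.

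Randomisation balances the arms at 80 and 80, but it does not balance the number of definite answers once *uncertain* is removed. A felt current in one arm and none in the other gives a concrete reason why certainty might differ. The rate then mixes differential certainty with differential belief. Two smaller faults add to this: any one of four unadjusted tests can trigger the failure verdict, and the success verdict has no criterion, since a non-significant result is not evidence that blinding worked.

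**Working it through.** **Inputs from the Protocol article.** 160 randomised 1:1, 80 per arm (Randomization and allocation). 20% dropout, so 160 × 0.80 = 128, or 64 per arm (Sample size calculation). Reference 50%, α = 0.05, four looks (Allocation and blinding). The article gives no expected guess rates, so every belief split and definite-answer count below is an assumption.

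**1. What 50% measures.** Let nA and nS be the definite answers in the active and sham arms, and qA and qS the shares of those saying *active*. The expected pooled correct rate is

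[nA·qA + nS·(1 − qS)] / (nA + nS).

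If nA = nS, this is 0.5 + (qA − qS)/2. Equal belief then gives exactly 50%, whatever the common level.

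**2. The stated level reproduces.** Exact one-sided binomial test at 50%: with 128 definite answers the critical count is 74 and the attained size 0.046; with 160 it is 91 and 0.048. Both are within 0.05.

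**3. Four looks, balanced counts, 50:50 guessing.**
- Nominal, independent weeks: 1 − 0.95^4 = 0.185.
- At attained size, independent weeks: 1 − (1 − 0.0463)^4 = 0.173 (n = 128); 1 − (1 − 0.0483)^4 = 0.180 (n = 160).
- Simulated with latent within-person correlation 0.5 or 0.8: about 0.12–0.16.
- If 80% of both arms say *active*: about 0.05–0.07. If 90%: about 0.01.

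**4. Unequal counts** (exact convolution of two binomials, one look).
- 72 versus 48, 80% saying *active* in each: (72×0.8 + 48×0.2)/120 = 67.2/120 = 56.0%. Critical count 70; flagged 30% of the time, and 57–76% over four looks. With the counts reversed (48 versus 72) the rate is (38.4 + 14.4)/120 = 44.0%, flagged less than 0.1% of the time.
- 40 (90% *active*) versus 72 (65%): (40×0.9 + 72×0.35)/112 = 61.2/112 = 54.6%. Critical count 66; flagged 17% of the time, and 37–45% over four correlated looks. Fisher's exact test of the *active* share between arms, on the same definite answers, has 84% power at one look. With the counts reversed (72 versus 40) the rate is 78.8/112 = 70.4%, flagged more than 99.9% of the time.

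In each pair, reversing the counts changes the result while the belief splits stay fixed.

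**5. The same examples with *uncertain* kept,** assuming all 80 per arm answer. Bang's index for an arm is (correct − incorrect)/all answers.
- First example: *active* 57.6/80 = 72% versus 38.4/80 = 48%; *uncertain* 10% versus 40%. Index +0.54 in active, (9.6 − 38.4)/80 = −0.36 in sham.
- Second example: *active* 36/80 = 45% versus 46.8/80 = 58.5%; *sham* 5% versus 31.5%; *uncertain* 50% versus 10%. Index +0.40 in active, (25.2 − 46.8)/80 = −0.27 in sham.

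Both patterns are visible by arm. In the second, the *active* share alone would mislead, so all three answers are needed.

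**6. Where the rule works.** With 64 versus 64 definite answers, it has 80% power per look for a belief difference of about 0.22, and flags 90% versus 50% with probability 0.9997.

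**Sidedness.** The test is worded directionally, while Statistical methods says "All tests will be two-sided, with a significance level of *α* = 0.05 unless otherwise specified for multiple comparisons". The figures above use the directional reading. Read two-sided, the independent any-of-four rate in step 3 is 0.081 (n = 128) or 0.092 (n = 160).

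**The case against.** The strongest reply is that the check would work in the scenario most to be feared. If participants who feel current know it and those who feel nothing know that too, the pooled rate rises well above 50% and is flagged. That stands.

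Three stronger readings are tempting and are not supported.

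- *The rule flags failure when beliefs are equal.* With unequal definite counts, belief is equal only among those who gave a definite answer. Step 5 shows the first example is 72% versus 48% saying *active* once *uncertain* is kept. In a sharper case, 60 versus 30 definite answers at 80%, it is 48/80 = 60% versus 24/80 = 30% (Fisher p = 0.0002). A flag there is arguably right; the fault is that the pooled rate cannot say what it found. With equal counts, false flags come only from the error level and the four looks.
- *The rule will miss unblinding caused by the felt current.* The missed case needs the arm that feels current to be the less certain one, and the article gives no reason to expect that. Four looks also raise detection as well as false alarms.
- *The article hides a weak sham and should be relabelled assessor-blinded.* Allocation and blinding says the check cannot replace a credible sham, Limitations repeats this, and Future directions calls for better-matched shams. This is a disclosed weakness, so relabelling would be a preference.

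It is also fair that *uncertain* rates are to be reported, that a false flag leads only to a cautious interpretation and a stated limitation, and that the check does not enter the primary analysis of VO2peak at T1. None of this repairs a verdict rule that the text fixes explicitly.

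**Conclusion.** The concern holds in a limited form. The decision rule can mislead when definite-answer counts differ between arms, because the pooled rate then moves with certainty as well as belief. The illustrated size is 30% flags per look for equal belief among definite answers at 72 versus 48, and 17% for a 25-point gap at 40 versus 72. These rest on assumed counts and splits, and the two cases need opposite imbalances that the article gives no means of predicting. The four looks cost up to about 17–18% false flags under independence, about 12–16% under correlation, and less when most participants say *active*. The near-50% success rule has no margin and so no defined meaning.

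With balanced counts the single test is valid, and gross unblinding would almost surely be detected. The weakness affects how a VO2peak result can be interpreted; it does not affect the primary estimate or its test.

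**What to change.** Keep the weekly question and its three answers, and change only the analysis and wording under Allocation and blinding, with the matching sentences in Limitations:

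1. Replace the pooled verdict with Bang's blinding index in each arm, keeping *uncertain* in the denominator, with 95% confidence intervals.
2. Report the between-arm differences in the proportions answering *active*, *sham* and *uncertain*, each with a 95% confidence interval.
3. Name one primary week in advance (the end of week 4 would be natural) and show the other weeks descriptively. If all four must carry a test, 0.05/4 = 0.0125 per look keeps the any-flag rate at or below 0.05.
4. Delete the rule that a rate near 50% means success.
5. Say that participants are *intended* to be blinded, with a cross-reference to the sham limitation already disclosed in the same section and in Limitations.

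The cost is slightly more analysis and a possibly less favourable blinding report. No new data are needed.

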### Intervention

A transcutaneous auricular vagus nerve stimulation device manufactured by Jiangxi Jingyi Medical Technology Co., Ltd., China, will be used. Stimulation electrodes will be placed over the vagus nerve distribution hotspot in the left auricular concha (23, 24). The stimulation parameters are: biphasic square wave, frequency 25 Hz, pulse width 200 µs, single session duration 30 min (25). The stimulation intensity will be individually adjusted based on each participant's sensory threshold. The sensory threshold is defined as the minimum current intensity at which the participant first clearly perceives a tingling sensation on the skin surface (starting from 0.1 mA and increasing slowly). The stimulation intensity in the active taVNS group will be set at a level that is just at or slightly above the sensory threshold (i.e., an intensity that the participant can clearly perceive without pain), typically between 0.5 and 1.5 mA, to ensure a clear, comfortable, and non-painful stimulation sensation. Treatment will be administered once daily, five days per week, for a total of 4 weeks. The sham stimulation group will use the same device, electrode placement, and operational procedures as the active stimulation group. Consistent with previous studies (25), the stimulation current will be set to 0 mA throughout the entire 30 min session. The indicator lights and buzzer sounds of the device will be synchronized with those of the active stimulation group throughout the treatment period.

Both groups will receive standardized conventional rehabilitation training delivered by the same rehabilitation team during the intervention period (weeks 1–4), consisting of 4 weeks, 5 days per week. The training includes: physical therapy (once daily, 40 min): positioning and transfer training (5 min), affected lower limb weight-bearing training (10 min), sit-to-stand transfer training (10 min), balance training (10 min), and walking training (5 min); and occupational therapy (once daily, 30 min): activities of daily living training (e.g., dressing, eating, grooming) and upper limb functional training. All training will be supervised one-on-one by uniformly trained therapists. Training intensity will be assessed every 5 days according to the patient's Brunnstrom stage and modified Barthel Index score, following an individualized progression principle. Training performance will be recorded in a standardized training log and reviewed weekly by the study coordinator. Adjustments to the duration of individual modules based on the patient's functional characteristics are permitted, provided the total duration remains unchanged; however, adding or removing training modules is not allowed. During the follow-up period (weeks 5–8), participants will continue to receive the same conventional rehabilitation training as in the intervention period (with unchanged content, frequency, and supervision), but will no longer receive taVNS or sham stimulation. Training performance will continue to be recorded and reviewed.

### Cardiopulmonary exercise testing

CPET will be performed at the Cardiopulmonary Exercise Laboratory of Shaanxi Rehabilitation Hospital at T0, T1, and T2. All tests will be conducted during the same time window between 9:00 a.m. and 12:00 p.m. A short (5–10 min) low-intensity familiarization session will be conducted 24–48 h before the formal baseline CPET to reduce learning effects. Participants will undergo a symptom-limited CPET on an electromagnetically braked cycle ergometer. For each participant, test conditions (ramp rate, seat position, foot fixation, and equipment configuration) will be kept identical at T0, T1, and T2, and verified by the same technician following a standardized protocol. A linear incremental ramp protocol will be used, with an increment rate of 5–10 W/min and a target test duration of 8–12 min. The specific rate will be selected based on baseline 6 min walk test performance: 5 W/min for ≤300 m, and 8–10 W/min for >300 m. For hemiparetic participants, the affected foot will be secured to the pedal using a fixation strap, and the seat position will be adjusted to approximately 5–10° of hip and knee flexion. If the participant cannot maintain 60 rpm, the cadence may be reduced to 50 rpm, with the actual cadence recorded. Asymmetric pedaling will be addressed through verbal encouragement for bilateral coordination. CPET operators will remain blinded to group allocation and time point. Verbal encouragement will be standardized using phrases such as “Please continue, keep up the rhythm” and “Two more minutes, well done,” with the number of encouragements recorded to ensure consistency across time points. Gas exchange parameters (VO_2_, VCO_2_) will be continuously measured using the breath-by-breath method, with simultaneous 12-lead electrocardiogram and blood pressure monitoring (every 2 min).

The safety termination criteria are: ischemic ECG changes, severe arrhythmias, or abnormal blood pressure (systolic ≥220 mmHg or diastolic ≥110 mmHg). The effort/quality reference criteria (which do not trigger immediate termination) include: respiratory exchange ratio (RER) ≥1.10, heart rate ≥85% of predicted maximum, or appearance of a VO_2_ plateau. The predicted maximum heart rate will be calculated using the formula: HRmax = 220 − age. For patients taking beta-blockers, or those with atrial fibrillation, or post-stroke autonomic dysfunction, the 85% predicted heart rate criterion may not be applicable; in such cases, effort adequacy will be assessed based on a combination of VO_2_ plateau, RER, and the reason for termination, rather than relying on a single heart-rate criterion. Inability to maintain pedaling rate is also a termination indicator. After test termination, the reason for termination will be recorded according to the following classification: cardiopulmonary limitation, neurological or motor limitation, musculoskeletal limitation, safety-related termination, or technical failure. The primary outcome is VO_2_peak, calculated as the average value over the final 30 s before termination. Gas and flow sensors will be calibrated before each test. Data will be acquired and stored using the dedicated SpiroPerfect cardiopulmonary exercise testing software.

VO_2_peak will be reported both as an absolute value (L/min) and relative to body weight (mL/kg/min). For tests terminated prematurely due to symptoms, the average VO_2_ over the final 30 s before termination will be taken as VO_2_peak, and the reason for termination will be recorded. Invalid tests due to non-physiological reasons will be repeated within 48 h. The proportion of participants meeting the criteria for adequate effort, peak work rate, exercise duration, and the reason for termination will be reported to comprehensively assess test quality. The ventilatory threshold will be analyzed as an exploratory outcome when data permit. Adequate effort will be determined based on a combination of VO_2_ plateau, respiratory exchange ratio, heart rate response (≥85% predicted), exercise duration, and the reason for termination, to avoid misclassifying effort as insufficient based on a single criterion (e.g., RER < 1.05). The primary analysis will follow the intention-to-treat principle, with missing data handled using multiple imputation. In the per-protocol analysis, participants who fail to achieve maximal effort (respiratory exchange ratio <1.05 or heart rate <85% of predicted) will be excluded as a sensitivity analysis.

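### A scripted encouragement phrase announces a remaining time in a symptom-limited exercise test that has no planned end, which puts an avoidable time cue on the primary endpoint

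*Protocol article*

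**What the plan says.** All of this is in the Protocol article, mainly under Cardiopulmonary exercise testing.

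- Type of test: "Participants will undergo a symptom-limited CPET on an electromagnetically braked cycle ergometer".
- Ramp: linear, "with an increment rate of 5–10 W/min and a target test duration of 8–12 min".
- Repeat tests: "test conditions (ramp rate, seat position, foot fixation, and equipment configuration) will be kept identical at T0, T1, and T2".
- Encouragement: "Verbal encouragement will be standardized using phrases such as “Please continue, keep up the rhythm” and “Two more minutes, well done".
- What is recorded about the encouragement is a count: "with the number of encouragements recorded to ensure consistency across time points".
- Operators: "CPET operators will remain blinded to group allocation and time point".
- Ending the test: "The safety termination criteria are: ischemic ECG changes, severe arrhythmias, or abnormal blood pressure". Inability to hold the pedaling rate is a further termination indicator. No time limit is given.
- Recorded reason for ending: five classes (cardiopulmonary, neurological or motor, musculoskeletal, safety, technical).
- Endpoint: "The primary outcome is VO_2_peak, calculated as the average value over the final 30 s before termination".

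The same section says that the proportion with adequate effort, peak work rate, exercise duration and reason for termination will be reported, and that participants with low RER or low heart rate are excluded in a sensitivity analysis. Statistical methods adds an analysis of those who meet the adequate-effort criteria.

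**The concern.** A symptom-limited ramp ends when the participant can no longer continue or a listed criterion is met. The operator cannot know that two minutes remain, so a phrase that says so either has no basis or refers to some expected finish. The only duration in the text that could serve as one is the 8–12 min target, although the document does not make that link.

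The primary endpoint is read from the last 30 s, so whatever influences the moment of stopping acts directly on it. With a fixed ramp, the same stopping time gives the same final work rate. If a participant treats the announced time as the finish at T0 and again at T1, a gain in fitness between the visits would largely not appear in VO2peak. Such tests add little or nothing to the treatment difference and dilute it.

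The recorded data would not identify these tests. The count of encouragements does not show which phrase was used, when, or on what trigger, and a stop at an announced time has no class of its own.

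**Working it through.** **1. Does the text contradict itself?** Side by side: the test is symptom-limited; the grounds for ending it are ECG changes, arrhythmia, blood pressure and loss of pedaling rate; 8–12 min is a target stated with the ramp rates. None of these gives the operator a known end. The scripted phrase presupposes one. The phrase and the type of test do not fit together.

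**2. What is two minutes worth on the ramp?**
- From the document: 5 W/min for the slower group, 8–10 W/min for the faster. Work = rate × 2 min, so 10 W at 5 W/min, 16 W at 8 W/min and 20 W at 10 W/min.
- Assumed, not in the document: 10 mL O2/min per W and 70 kg. VO2 change = W × 10 / 70, which is 10 × 10 / 70 = 1.4 and 20 × 10 / 70 = 2.9 mL/kg/min.
- Range for 8–12 mL/min per W and 60–80 kg: from 10 × 8 / 80 = 1.0 to 10 × 12 / 60 = 2.0 at 5 W/min, and from 20 × 8 / 80 = 2.0 to 20 × 12 / 60 = 4.0 at 10 W/min.

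This is the shift in one person's test if the stop moves by two minutes. It is not a shift in a group mean.

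**3. Yardstick for power.** Sample size calculation uses f = 0.25 and f = d/2, so d = 0.50, with about 64 per group before dropout. A two-sided two-sample t-test at 0.05 with 64 per arm and d = 0.50 has power 0.801, in line with the planned 0.80. The plan names a repeated-measures module; the two-sample test is used here only because the primary effect is the group difference at T1.

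**4. Dilution, as an illustration.** Let p be the share of tests, equal in both arms, that end on the cue and show no treatment difference, with the SD unchanged. Then d becomes 0.50 × (1 − p). The last column allows for baseline adjustment with the plan's correlation of 0.50: d is divided by √(1 − 0.50²) = 0.866.

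| p (assumed) | d | Power, unadjusted | Power, baseline-adjusted |
|---|---|---|---|
| 0 | 0.50 | 80% | 90% |
| 10% | 0.45 | 71% | 83% |
| 20% | 0.40 | 61% | 74% |
| 30% | 0.35 | 50% | 62% |

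The document gives no value for p, and none can be derived from it.

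**5. Added noise.** Suppose instead that the phrase is used inconsistently and shifts a random half of the T1 tests by δ. With an assumed SD of 4 mL/kg/min (d = 0.50 is then 2 mL/kg/min), the new SD is √(16 + 0.25 δ²):
- δ = 1.43: SD 4.06, power 79%
- δ = 2.0: SD 4.12, power 78%
- δ = 2.86: SD 4.25, power 75%

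The loss from noise alone is small, from 80% to 75–79%.

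**The case against.** The strongest reply is that nothing in the document lets the clock end the test. The target duration is no stopping rule, and the timed phrase is one example, listed beside a plain request to continue. It can be heard as a prompt to keep going, which would lengthen tests. Dilution needs several steps that the text does not state: the phrase comes at a similar elapsed time at each visit, the participant still has reserve, and the participant stops on cue. A rider who stops with reserve would tend to show a low RER, a low heart rate or no plateau, and the effort reporting and the adequate-effort analyses would pick up part of this. Operators are blinded to group and time point. The full operator script may also sit in a testing procedure that the article condenses.

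Most of this stands, and it limits the point to a possible loss. It does not remove it. The phrase is stated text, not an omitted detail. Blinding guards against a difference between arms but not against dilution common to both. The effort checks are reporting items and sensitivity analyses; cue-ended tests stay in the primary analysis.

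Two stronger readings are tempting and are not supported. One is that the clock sets the end of the test and hides a treatment effect: no rule makes time a stopping criterion, and the share of affected tests is unknown. The other is that inconsistent use of the phrase adds noise as large as the planned effect: that sets one person's shift (1.4–2.9 mL/kg/min) against a difference between group means, and step 5 of the working shows the real cost to be a few points of power.

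**Conclusion.** The point holds as a minor design flaw in how the primary endpoint is measured. A phrase that announces a remaining time does not belong in a symptom-limited ramp, and with a final-30-s endpoint on a fixed ramp any influence on stopping goes straight into VO2peak. The likely direction, if participants pace to or stop at the announced time, is towards no difference at T1; bias in favor of one arm is unlikely. The size is unknown. The power figures of 71%, 61% and 50% rest on assumed shares of 10%, 20% and 30% with exactly no effect and on an unadjusted test, and are higher with baseline adjustment. They show what could be lost, not what this trial will lose.

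**What to change.** Under Cardiopulmonary exercise testing, replace the timed phrase with an untimed one, so that the standardized script contains untimed phrases only. Add a sentence that elapsed time, remaining time and target duration are neither told nor shown to the participant during the test at any visit. The grounds for ending the test, the safety monitoring and the analysis stay as they are.

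The cost is a change of wording and a short operator briefing. Recruitment is planned to start in July 2026, so the change can be in place before the first baseline test and apply equally at T0, T1 and T2.
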